#### Caregiver report measures

Caregivers’ reports of children’s expressive vocabulary will be measured using the MacArthur Bates Communicative Development Index—Computer Adaptive Test (CDI-CAT) in their first and final visits [27]. The CDI-CAT is normed for ages 15 to 36 months based on 25–50 questions in English or Mexican Spanish and takes about 5 minutes to complete. The CDI-CAT was developed based on 7,633 English-speaking children 12–36 months and 1,692 Spanish-speaking children 12–30 months based on three Communication Development Inventories (CDI) and found the item response theory models had a correlation of 0.92 with the full CDI forms [28].

#### Observational measures

In addition to clinician-administered measures, we will include a parent-child interaction observation using structured tasks to elicit a naturalistic child language sample [29–35]. These interactions will be recorded, transcribed, and coded to assess the number of clear and intelligible utterances, unique words used, and mean length of utterance (MLU). Transcription staff will transcribe at least 10 practice recordings before reviewing study videos. A “gold standard” staff person will independently review at least 20% of the video-recordings after that to monitor for drift. Similarly, before coding transcripts, staff in training will code practice transcripts to establish reliability. After that, two staff will independently code 20% of the transcripts to monitor inter-rater reliability.

### Secondary outcome measure

#### Speech production accuracy and sound diversity

Speech sound production skills are often a concern for children with CP±L, particularly in early childhood. Although data on the effects of DBS interventions on speech are lacking, studies by Scherer et al. suggest benefits for caregiver-focused interventions and scaffolded practice [10–12]. Further, we hypothesize that differences in speech sound production at baseline may influence caregivers’ responses to child vocalizations. For example, some of the core skills in DBS (e.g., reflecting and expanding on the child’s language) may be more challenging when a child has a speech sound disorder. We, therefore, plan to assess speech production skills at baseline and again at the end of treatment. We will use a structured picture naming task developed for this study using around 25 images that children either name or repeat in English, Spanish, or both. The single-word stimuli were selected based on the consonants expected in a child’s sound inventory for each language for ages 24–40 months [36]. Each consonant phoneme will be sampled in at least two positions of stimulus words (initial and final for English, initial and medial for Spanish) to allow for computation of percent consonants correct-revised scores (PCC-R) and to derive a total number of unique consonants produced, serving as an estimated consonant inventory [37, 38]. Speech samples will be video recorded and later transcribed by two speech-language pathologists (SLP) with extensive experience evaluating speech in children with cleft palate. A bilingual SLP will code Spanish-speaking and Spanish-English bilingual children’s samples. We will re-code 20% of samples for intra-rater and inter-rater reliability. Samples will be analyzed in batches, including a random assortment of videos from pre- and post-treatment to minimize bias.

### Intermediate and exploratory outcomes

Throughout the study, we will use observational coding of parents’ book-sharing videos to assess the quality and frequency of book-sharing interactions in the BOOST and SOC groups. These are proximal targets for the intervention, hypothesized to mediate changes in children’s language outcomes. We also plan to code children’s language during book-sharing interactions, exploring whether intervention changes children’s vocalizations (e.g., number of unique words used, mean length of utterance) during reading.

#### Quality of book-sharing interactions

The quality of parent-child interactions during book sharing will be measured by observational coding of participants’ videos at baseline and throughout the intervention. We plan to use an observational coding system based on previous DBS studies and studies of parent-child interactions. The coding reflects observation characteristics (e.g., length, audio quality of video) and parents’ use of DBS strategies, sensitivity, and engagement. Items are rated on 30-second intervals, indicating whether each behavior occurred during the interval. An overall score will be generated, with higher scores indicating better engagement and use of DBS skills.

#### Frequency of book-sharing interactions

The frequency of book-sharing interactions will be tracked via parent reports. We will use an ecological momentary assessment (EMA) approach, sending surveys on a randomly selected five days each week and asking parents (1) whether they read to their child in the last 24 hours, (2) how many books they read, and (3) the book titles. We will generate an average score for each participant, reflecting how many books the parent reports reading to their child daily.

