**Objectives:**

The study will test two primary hypotheses. First, toddlers randomized to BOOST will exhibit better language outcomes than children receiving standard-of-care (SOC). Second, we hypothesize that the BOOST program’s effect on language outcomes is mediated by the frequency and quality of parent-child reading interactions.

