### Intervention

All participants will receive five age-appropriate children’s books that they will be encouraged to read with their children. We will ask participants in both groups to video record themselves reading these books with their children and complete surveys of shared reading frequency. Families will use a study app to securely upload book-sharing videos with the research team. This will help to control for possible effects related to being observed. Children will continue to receive SOC treatment, including speech-language therapy and developmental interventions at enrollment or initiated during the study, and follow up with their craniofacial providers.

Participants randomized to the BOOST intervention group will receive support and encouragement to promote shared reading and dialogic book-sharing skills. During the study protocol development phase, we pilot-tested the BOOST program with 40 families recruited from participating centers and made minor modifications based on parent and interventionist feedback. The program is delivered in three 50-minute live, face-to-face telemedicine (Zoom) visits scheduled every 2–3 weeks. The BOOST program encourages parents to increase the frequency of shared reading, introduces skills to promote child engagement and involvement in reading, and offers strategies to promote language development. Depending on parents’ preference, we will provide English or Spanish teaching materials for each of the key skills taught. Interventionists will review the book-sharing videos parents upload between sessions to identify parent strengths, application of target skills, and opportunities for improvement.

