We will use a multi-step linear regression approach to examine whether changes in parents’ reading behaviors mediate differences in children’s language outcomes. Mediators include: (1) shared reading frequency, (2) overall quality of parent-child interactions, and (3) parents’ shared reading skills, which will be assessed throughout the intervention period. Mediators will be analyzed separately to determine their individual effect on child outcomes and to avoid a washout effect from including all mediators in a single model. We will not adjust for multiple comparisons for this aim. Each regression model will follow the same basic approach to analyzing the effects of adjustment for a given mediator (Z) on the association between the intervention (X) on the child language outcome (Y). We will run two models per outcome: (1) Y = α + βX + e1, and (2) Y = A + BX + CZ + e2. The terms e1 and e2 represent model errors. Model 1 describes the unadjusted effect of the intervention on the outcome. Model 2 illustrates the combined effect of intervention and mediator on outcome. A comparison of the coefficients β and B indicates the degree of mediation. For example, β = B >0 suggests a positive intervention effect that is not mediated by Z (i.e., the null hypothesis of no mediation), whereas β >0 and B = 0 reflects a positive effect fully mediated by Z. Intermediate values reflect the degree of mediation (e.g., B = β/2 represents 50% mediation). Confidence intervals for the degree of mediation will be obtained using the bootstrap methods.

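### Reading frequency, a mediator in the second primary hypothesis, is reported by unmasked parents whom only BOOST coaches to read more, so a reporting shift tied to arm would inflate the mediated share

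*Protocol article*

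**What the plan says.** The abstract's Objectives state: "The study will test two primary hypotheses". The second is that the effect on language is "mediated by the frequency and quality of parent-child reading interactions". Statistical methods lists three mediators, analysed separately: reading frequency, overall quality of the interaction, and parents' shared reading skills. Each is entered as Z in Model 2, and the result is read as follows: "A comparison of the coefficients β and B indicates the degree of mediation".

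On measurement, the section on frequency says: "The frequency of book-sharing interactions will be tracked via parent reports". It describes "sending surveys on a randomly selected five days each week", with questions about reading in the past 24 hours, the number of books and their titles. The score is a daily average, "reflecting how many books the parent reports reading to their child daily".

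On what each arm is told, the Intervention section says all families receive five books "that they will be encouraged to read with their children", and both arms upload videos and answer the same surveys. It then says of the active arm: "The BOOST program encourages parents to increase the frequency of shared reading". The Randomization section gives the comparison arm no sessions. Masking there covers staff who assess or code outcomes. No masking of parents is described, and none would be possible.

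The opening of Intermediate and exploratory outcomes says video coding will assess both quality and frequency. This disagrees with the frequency section that follows it.

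**The concern.** One arm is coached in live sessions to raise a quantity, and the same study then asks parents to report that quantity. Identical surveys in both arms equalise the effect of being surveyed, but not the effect of being coached. Some BOOST parents may round up, or count borderline occasions, because they know what the programme hopes to see.

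The planned rule cannot tell a change in reporting from a change in reading. Any between-arm difference in Z, multiplied by the slope of language on Z, is counted as mediation. The conclusion at stake is how BOOST works, in particular whether more frequent reading carries the benefit. Later programmes would use that conclusion to choose which component to keep.

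**Working it through.** The article gives no figure for the frequency mediator, so there is none to reproduce.

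**Inputs from the article.** Analysed sample 320 × 0.8 = 256, or 128 per arm. Total effect β = 0.4 SD, the design difference in the sample-size section, used here as an illustration.

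**Assumed, because the article gives neither.** C, the within-arm slope of language on reported frequency (SD per SD), is taken as 0.1 to 0.3. δ, the over-reporting in BOOST relative to the comparison arm, is taken as 0.2 to 0.5 SD and as constant across BOOST parents.

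**Step 1: what the rule measures.** With Model 1, Y = α + βX + e1, and Model 2, Y = A + BX + CZ + e2, least squares gives β − B = C·a, where a is the arm difference in mean Z.

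**Step 2: split the arm difference.** If a = (true change in reading) + δ, then β − B = C·(true change) + C·δ. The second term is the inflation. It vanishes if δ = 0 or C = 0, but hypothesis 2 itself presupposes C > 0.

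**Step 3: size of C·δ, and as a share of β = 0.4.**

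| C | δ = 0.2 | δ = 0.5 |
|---|---|---|
| 0.1 | 0.02 (5%) | 0.05 (12.5%) |
| 0.2 | 0.04 (10%) | 0.10 (25%) |
| 0.3 | 0.06 (15%) | 0.15 (37.5%) |

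**Step 4: if reading truly rises.** Take a true rise of 0.5 SD (assumed), C = 0.2 and δ = 0.2. Then β − B = 0.2 × 0.5 + 0.2 × 0.2 = 0.10 + 0.04 = 0.14. The reported share is 0.14/0.4 = 35%, against 0.10/0.4 = 25% without over-reporting. The finding is inflated, not invented.

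**Step 5: the extreme case of no true change.** Simulation of the two models with 128 per arm, β = 0.4, 200 trials per setting and 200 bootstrap resamples each gave these proportions of trials with the 95% interval for β − B wholly above zero:

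| C | δ = 0 | δ = 0.2 | δ = 0.5 |
|---|---|---|---|
| 0 | 0% | 0% | 4% |
| 0.1 | 0.5% | 11.5% | 33% |
| 0.2 | 3.5% | 30.5% | 93% |
| 0.3 | 2% | 40.5% | 96.5% |

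The simulated mean indirect effects agree with Step 3 (for example 0.105 against 0.10 at C = 0.2, δ = 0.5).

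**Step 6: what a correction over δ can show.** Replacing Z by Z − δX leaves C unchanged and turns β − B into C·(a − δ). The point estimate reaches zero at δ = a exactly, whatever the child outcome. Such an analysis is therefore informative only when read beside a and its interval.

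**The case against.** **Safeguards.** Recall over 24 hours on random days, with titles, is much harder to inflate than a global rating. The comparison arm is also encouraged to read the books, so only the difference in pressure between arms matters. This stands as a reason to expect a smaller δ. It does not make δ zero: titles are self-reported too, no use of them as a check is stated, and only one arm has sessions that press for more reading. Video counts cannot substitute, because Table 1 requests the five videos on a fixed schedule.

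**Missing analysis plan.** A sensitivity analysis for one mediator is commonly left to the analysis plan, which is not shown. That is right, and its absence from the article is not the point. The point is that the article itself fixes the measure, the mediator and the rule, and together these count a reporting shift as mediation.

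**Stronger readings.** A reader might infer from Step 5 that the trial is likely to declare wholly false mediation. The article does not support that: it gives neither C nor δ, and no true change is an extreme assumption. The Introduction cites improvement in parents' reading behaviours of about 1.0 SD, though not for frequency specifically. A reader might also infer that interventionists see the survey answers. The article says only that they review the videos.

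**Thresholds.** Requiring the finding to survive a fixed δ such as 0.3 SD would be arbitrary and costly. With SE = √(2/128) = 0.125, the observed difference must exceed 0.3 + 1.96 × 0.125 = 0.545. A wholly genuine rise of 0.4 SD passes with probability P(z > (0.545 − 0.4)/0.125 = 1.16), about 12%, even before uncertainty in C. This objection stands, and no threshold is proposed.

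**Conclusion.** The concern holds in a limited form. A reporting shift of δ in BOOST adds C·δ to the quantity the plan reads as the degree of mediation by reading frequency. Under the assumed ranges and β = 0.4 SD, that is 0.02 to 0.15 SD, or about 5% to 38% of the total effect. Whether it enlarges a real indirect effect or creates a false one depends on whether reading truly changes, which parent report alone cannot settle.

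The reach is narrow. The between-arm language comparisons do not use reported frequency, and quality and skills are coded from video by masked staff. The sensitivity analyses listed in Statistical methods address non-adherence, missing data, attrition, fidelity and community therapy, and the Limitations section does not raise reporting. This is an inexpensive improvement to one mediation claim, not a threat to the efficacy result.

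**What to change.** 1. Add the same line to the surveys in both arms, saying that interventionists do not see the answers, and keep that true in practice.
2. As a sensitivity analysis, report the indirect effect C·(a − δ) with its bootstrap interval over a range such as δ = 0 to 0.5 SD, beside the arm difference a in reported frequency and its interval. State that the point estimate reaches zero at δ = a, and set no pass/fail threshold.
3. Word the conclusion as mediation by parent-reported frequency, and rest claims about changed reading behaviour mainly on the masked video-coded mediators.
4. Reconcile the opening of Intermediate and exploratory outcomes (frequency from video coding) with the frequency section (frequency from parent report).

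The cost is one extra analysis, a small change of survey text during enrolment, and a more cautious frequency claim. Design, sample size and the primary tests stay as they are. No interim outcome analyses are planned and enrolment runs to about April 2028, so this can still be specified before outcomes are analysed.

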#### Child language during book-sharing

We will transcribe book-sharing interactions using the video recordings shared by parents throughout the study. Child vocalizations will be coded for the number of clear and intelligible utterances, the number of unique words used, and the mean length of utterance (MLU).

### Sample size considerations and participant recruitment and retention

We determined the sample size (N = 320) based on the number of participants needed to ensure 80% power to test the hypothesis that children in the BOOST intervention group will have better receptive and expressive language skills than those in the SOC comparison group. Power analyses were based on two-sample unequal-variance t-tests, an alpha = 0.05/2 to adjust for multiple comparisons, and up to 20% attrition (i.e., final N~256). Under these assumptions, we will have 80% power to detect treatment group differences of >0.4 SD for our primary outcomes. Treatment effects this large have been observed in DBS studies with other non-cleft populations and are considered plausible and clinically meaningful [13].

Our assessment of longitudinal changes in child language during book-sharing interactions (Hypothesis 1b) will use a generalized estimating equations (GEE) approach to linear regression with robust standard error estimates. The outcome for these analyses will be observed child language, calculated as an average number of utterances, unique words used, and mean length of utterance. Analyses will test the effects of the intervention on children’s language during book-sharing interactions over the five observations. We will have > 80% power to detect changes with an effect size > 0.4 between any two time points and changes with effect sizes > 0.3 overall. Meta-analyses of similar interventions with non-cleft participants suggest that effect sizes this large or larger are observed and considered clinically meaningful. Similarly, we will have > 80% power to assess longitudinal changes in children’s language during book-sharing interactions, the quality and frequency of book-sharing interactions, and changes in parents’ book-sharing behaviors as a mediator of differences in children’s language outcomes.

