The BOOST program was developed for remote delivery to accommodate geographically dispersed families. We will meet with families for three 50-minute treatment sessions via Zoom to discuss the application of DBS strategies. Parents will record and share videos of themselves reading with their children between visits. These videos will be used for the intervention (e.g., to identify and reinforce caregiver strengths) and to assess adherence and changes in parents’ reading behaviors. Parents will also complete surveys to evaluate the frequency of shared reading. We will compare children in the BOOST group to children in a group that will receive SOC plus the same books shared with participants in the treatment group. Parents in the SOC group will be asked to upload videos of shared reading and complete shared reading frequency surveys. These procedures will help control the effects of having access to age-appropriate children’s books and being observed.

We hypothesize that (1a) children in the BOOST group will exhibit better expressive and receptive language than children in the SOC group at an end-of-study assessment; (1b) children in the BOOST group will exhibit better language than children in the SOC group during shared reading interactions (e.g., more utterances, more unique words used, larger mean length of utterance); and (2) differences in child language outcomes will be mediated by increased frequency of book-sharing and improvements in the quality of parent-child book-sharing interactions. The study will use a multi-center, parallel-group, randomized controlled trial (RCT) design. We will randomize half of the participants to the BOOST group and half to the SOC comparison group. Parents’ use of target skills will be observed and coded throughout the intervention period, and children’s language outcomes will be assessed at least eight weeks after the end of treatment. Staff involved in observational coding and child outcomes assessment will be unaware of children’s randomization.

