Our primary outcomes are children’s expressive and receptive language. Based on studies of children without orofacial clefts, DBS interventions result in moderate improvement in both domains, usually measured using single-word expressive and receptive vocabulary measures [13]. We have incorporated multiple assessment methods for these outcomes, including standardized clinician-administered measures, parent report measures, and observational coding of naturalistic language samples. Staff completing all outcomes assessments will be unaware of children’s randomization. Project staff completing standardized measures will be asked to practice and record an assessment with a non-study child in the target age range. These administrations will be reviewed by one of the investigators (AJ) and scored for reliability before certifying examiners to test RCT participants. During the study, we will video record every tenth administration for reliability scoring. Similarly, staff completing observational coding will practice on sample videos with scores compared to a "gold standard" (LS) to ensure reliability before coding videos for RCT participants. During the study, at least 20% of observations will be coded by more than one observer to assess inter-rater reliability.

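### The stated 80% power is a per-domain figure attached to a hypothesis worded for both language domains, and the fixed 0.05/2 split could be replaced by Holm without cost

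*Protocol article*

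**What the plan says.** The Introduction states Hypothesis 1a as "children in the BOOST group will exhibit better expressive and receptive language than children in the SOC group at an end-of-study assessment". The section on study assessments says "Our primary outcomes are children’s expressive and receptive language". The sample-size section ties N = 320 to the same two-part hypothesis: the number was chosen to "ensure 80% power to test the hypothesis that children in the BOOST intervention group will have better receptive and expressive language skills". It then gives the basis. "Power analyses were based on two-sample unequal-variance t-tests", with "an alpha = 0.05/2 to adjust for multiple comparisons" and up to 20% attrition, leaving about 256 children. The result is put as "we will have 80% power to detect treatment group differences of >0.4 SD for our primary outcomes".

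The Statistical methods section specifies unadjusted unequal-variance t-tests for the post-intervention comparison. The article gives neither a correlation between expressive and receptive scores nor a power figure for the two domains together.

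**The concern.** The hypothesis and the alpha belong to different decision rules. If the aim is to show a benefit in both domains, no alpha split is needed, because requiring two significant tests cannot raise the false-positive rate. If the aim is a claim for each domain on its own, a split or another multiplicity procedure is needed, but then the hypothesis should not read as a conjunction and 80% is the power for each part of it.

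Two things are at stake. First, a reader may take the 80% as the chance of confirming Hypothesis 1a as worded, which it is not. Second, when only one domain is significant, the hypothesis wording and the alpha rule invite different summaries of the trial. Apart from the wording, a fixed 0.025 for both tests gives up power that a step-down procedure keeps at the same family-wise error.

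**Working it through.** **Inputs from the article.** N = 320, allocated 160 and 160; 20% attrition, so 320 × 0.8 = 256, or 128 per arm; effect 0.4 SD; alpha 0.05/2 = 0.025 per test.

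**Assumptions.** Two-sided tests (the article attributes the division by 2 to multiple comparisons and does not mention sidedness); one primary test per domain; a true effect of 0.4 SD in both domains; correlation ρ between the two test statistics from 0 to 0.9.

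**Step 1: reproduce the plan's figure.** Noncentrality = d·√(n/2) = 0.4 × √(128/2) = 0.4 × 8 = 3.2, with 2 × 128 − 2 = 254 degrees of freedom.
- Two-sided 0.025: critical value 2.255, power 82.7% (noncentral t).
- Two-sided 0.05: critical value 1.969, power 89.0%.
- Effect detectable with exactly 80% power at 0.025: 0.387 SD, which rounds to the stated 0.4.

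The stated 80% is therefore reproduced, slightly conservatively, as power for one outcome.

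**Step 2: power for the two domains together.** Treat the two test statistics as bivariate normal, each with mean 3.2 and variance 1, with correlation ρ. Let a = 3.2 − 2.255 = 0.945 and b = 3.2 − 1.969 = 1.231, let Φ be the normal distribution function, and let F(x, y) be the standard bivariate normal distribution function.
- Both significant at 0.025: F(a, a).
- At least one: 2Φ(a) − F(a, a).
- Exactly one: 2[Φ(a) − F(a, a)].
- Both under Holm (at least one p below 0.025 and both below 0.05): 2F(a, b) − F(a, a).
- Per domain under Holm: half the sum of at least one and both under Holm.
- Both at 0.05 each, with no split: F(b, b).

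By hand at ρ = 0: Φ(a) = 0.828 and Φ(b) = 0.891. Both at 0.025 = 0.828² = 0.685. Both under Holm = 2 × 0.828 × 0.891 − 0.685 = 0.790. At least one = 2 × 0.828 − 0.685 = 0.970. Per domain under Holm = (0.970 + 0.790)/2 = 0.880.

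| ρ | Both, 0.025 each | Exactly one, 0.025 each | At least one | Both, Holm | Per domain, Holm | Both, 0.05 each |
|---|---|---|---|---|---|---|
| 0 | 69% | 29% | 97% | 79% | 88% | 79% |
| 0.5 | 73% | 20% | 93% | 81% | 87% | 82% |
| 0.8 | 76% | 13% | 89% | 83% | 86% | 84% |
| 0.9 | 78% | 9% | 87% | 84% | 86% | 86% |

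The at-least-one column is the same under Bonferroni and Holm, because Holm's first step is the Bonferroni test. Using the normal critical values 2.241 and 1.960 in place of the t values moves every figure by less than one percentage point.

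**Step 3: error control under Holm.** If neither domain has an effect, a false claim needs the smaller p-value to be below 0.025, which has probability at most 2 × 0.025 = 0.05. If only one domain has no effect, a false claim needs that domain's own p-value to be below 0.05. The family-wise error is at most 5% in either case, whatever the correlation. Everything that Bonferroni rejects, Holm rejects too.

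**The case against.** The strongest reply is that nothing is miscalculated. The sentence that carries the power claim speaks of differences for the primary outcomes, in the plural. The arithmetic is that of a single test at 0.025, and the alpha split itself signals separate claims. The word joining the two domains may be no more than a list. That stands: the 80% is a correct per-outcome figure, and the fault lies in the hypothesis to which it is attached.

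Two stronger readings are tempting, and the article does not support either.
- **That the true power is about 73%.** That number needs a correlation of 0.5, which appears nowhere in the article, and a mixed rule (both domains required, yet each tested at 0.025) that the article never states. Under either coherent rule there is no material shortfall: at least one domain at 0.025 has 87% to 97% power, and both domains at 0.05 each have 79% to 86%. N = 320 is not shown to be too small.
- **That success is undefined when one test is significant.** A Bonferroni split already permits a claim for the significant domain and none for the other. What the wording leaves open is whether one positive domain confirms Hypothesis 1a as written, and the full protocol or analysis plan, which are not shown, may settle that.

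It is also fair to say that Bonferroni is valid and that preferring Holm is not the correction of an error. I agree, and offer it as an improvement. Finally, the article lists further measures under the primary outcomes (the parent-report vocabulary inventory and the language sample), so a family of exactly two tests is an assumption. It is the one implied by dividing alpha by 2.

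**Conclusion.** The point holds as a mismatch of wording together with an available gain, not as a power error. Hypothesis 1a and the sample-size statement are conjunctive; the 0.05/2 split and the 80% belong to separate claims per domain. Per-domain power at 0.4 SD is about 83%. Power to show both at 0.025 each would be about 69% to 78%, with exactly one domain significant in about 9% to 29% of trials. Holm raises power for both to about 79% to 84% and per-domain power to about 86% to 88%. These ranges assume 128 per arm, equal true effects of 0.4 SD in both domains, two-sided tests, one primary test per domain, and correlations from 0 to 0.9.

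**What to change.** 1. In the sample-size and Statistical methods sections, replace the fixed 0.05/2 with the Holm step-down over the two primary tests: the smaller p-value is tested at two-sided 0.025 and, if it is significant, the other at 0.05.
2. Reword Hypothesis 1a, and the matching sentence on sample size, as a benefit in expressive and/or receptive language, with a separate claim for each domain that is significant.
3. Label the 80% as per-outcome power. If power under Holm is added, give it at 0.4 SD as about 86% to 88% per domain, 79% to 84% for both and 87% to 97% for at least one, stating the correlation range of 0 to 0.9 and the assumption of one primary test per domain.

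The cost is wording in the protocol and analysis plan: no extra participants, no new data and no loss of error control. The article puts the end of enrollment at about April 2028 and plans no interim analyses of the outcomes, so the change can be made and dated before any outcome comparison is seen.
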